# Justification

This trial will generate important public health information on the efficacy of IPTi in preventing anemia and clinical malaria among infants in an area with intense malaria transmission and ongoing prevention efforts through the use of insecticide treated nets. This trial will contribute towards understanding the mechanism of action through which IPTi achieves reduction in anemia and clinical malaria (i.e. through intermittent clearance of parasites vs. a chemoprophylactic effect afforded through the use of an antimalarial with a long half-life). The information gained will be useful to decide what sort of antimalarials are appropriate for IPTi, and ultimately will help to direct child survival and malaria control policy in African countries. If alternative drug regimes to SP prove effective, that information will be valuable to policymakers as levels of *P. falciparum* resistance to SP rise with increased usage in east Africa.

Information from this study may prove useful to policymakers at WHO, UNICEF, and the Kenya MOH for evaluating the safety of IPTi, particularly with relation to response to EPI vaccines.

**Objectives**

## Primary objective

Compare the efficacy of iron supplementation and IPTi with one of 3 antimalarial regimens (SP/AS3, Lapdap [chlorproguanil-dapsone], or AQ/AS3) given at routine EPI visits with iron supplementation alone (+ placebo) on the prevention of clinical malaria in the first year of life.

## Secondary objectives

1. Compare the efficacy of iron supplementation plus IPTi with one of 3 antimalarial regimens (SP/AS3, Lapdap [chlorproguanil-dapsone], or AQ/AS3) given at routine EPI visits with iron supplementation alone (+ placebo) on the prevention of moderate and severe anemia in the first year of life.
2. Assess the impact of IPTi with the aforementioned regimens on serologic responses to EPI vaccines (Polio, Diphtheria, Tetanus, Pertussus, Hepatitis B, *Hemophilus Influenzae* type B, and Measles).
3. Assess the impact of IPTi with the aforementioned regimens (particularly SP/AS3) on the nasal carriage rates of *Haemophilus influenza* type b.
4. Compare the efficacy of iron supplementation and IPTi with one of 3 antimalarial regimens (SP/AS3, Lapdap [chlorproguanil-dapsone], or AQ/AS3) given at routine EPI visits with iron supplementation alone (+ placebo) on the prevention of all-cause hospitalization in the first year of life.

# Design and Methods

## Study Design

We propose to conduct a double blind, placebo controlled, randomized controlled efficacy trial (RCT) among children under longitudinal observation to examine the above-mentioned questions. Children will be recruited during the first EPI visit at 6 weeks of age and will be followed prospectively with collection of epidemiologic, clinical, and laboratory data. Routine EPI visits in Kenya occur at 6, 10, and 14 weeks, and again at 9 months of age. IPTi will be provided under supervision at 10 and 14 weeks and again at 9 months with one of 3 drug regimens or placebo. From ages 2-6 months, supplementation with ferrous sulfate will be given as part of the intervention package.

The 4 arms of the study are as follows

I Intermittent SP/AS3 treatment with daily iron supplementation

II Intermittent Lapdap treatment with daily iron supplementation

III Intermittent AQ/AS3 treatment with daily iron supplementation

IV Intermittent placebo treatment with daily iron supplementation

## Study site

The study will take place in Asembo (Rarieda Division), western Kenya; the total population is approximately 55,000 persons in 76 villages over 200 square kilometers. If there is difficulty in recruiting the full cohort from Asembo, one clinic from neighboring Gem (wagai division, total population approximately 56,000 persons in 105 villages over 172 square kilometers) may be added. This is an area of intense perennial transmission. Entomological inoculation rates in this part of western Kenya were once high, ranging from 237-299 infective bites per person per year.[47]. At present, the high rate of coverage with ITNs has reduced the EIR to approximately 10 infective bites per person per year. Although transmission is perennial, there are two rainy seasons and therefore some seasonal variation in transmission intensity.

In western Kenya, pediatric mortality rates continue to be very high; 32/1,000 live births for neonates, 176/1,000 live births for infants, and 257/1,000 live births for children < 5 years of age.[48] Based on the results of an ITN study in this area, it is estimated that approximately 20% of infant deaths are malaria-related ([name], Centers for Disease Control, and [name], personal communication).

ITN ownership and usage rates are high in the study area following several years of intense distribution as part of a research study. Nearly 100% of households have an ITN, and usage has been estimated at 70% ([name], Centers for Disease Control and Prevention and [name], personal communication).

EPI coverage in Nyanza province is moderate: 91-92% of children receive the first dose of diphtheria pertussis tetanus vaccination (DPT) and oral polio vaccination (OPV), 80-82% receive the second doses of those two vaccines, and 66% receive the third dose. Measles vaccination, given at 9 months of age, is received by 62% of children. [49] These data have recently been confirmed through a cross-sectional survey in the study area showing a rate of 79.4% for the second dose of DTP and OPV. The normal immunization schedule is BCG immunization soon after birth, DTP and OPV at 6, 10 and 14 weeks of age, and measles vaccination at 9 months. Recently (December, 2001), the Kenya MOH began administering a pentavalent vaccine (diphtheria, tetanus, pertussis, hepatitis B, and Hib) in place of DTP. All clinics in the study area now use this vaccine; the vaccination schedule has remained the same.

SP has been used extensively in trials in the study area since 1992; SP was adopted as first line therapy by the Kenya MOH in 1998. Recent data suggest that there is parasitologic treatment failure rate of approximately 28% at day 7 among children < 2 years of age treated with SP ([name] [name], Centers for Disease Control, personal communication).

CDC has a longstanding collaboration with the Center for Vector Biology and Control Research, KEMRI in Kisumu, and there is an excellent research infrastructure already in place. There is full-time CDC staff employed at the KEMRI-CDC research station. In addition, there is a demographic surveillance system in place that may allow for the measurement of impact of a study intervention on mortality.

The area is served by 2 district hospitals (Bondo and Kisumu) between 10 and 60 km from the study area, and 1 mission hospital. There are 6 peripheral health units located in Asembo. These units are comprised of government, community, private, and mission facilities, and are normally staffed by an enrolled community health nurse. Only one of the peripheral health units currently has diagnostic facilities for malaria.

## Demographic Surveillance System

A demographic surveillance system (DSS) is a process that involves continuous monitoring of a geographically defined population to generate high quality, population-based, longitudinal health and demographic data. A well-developed DSS can provide two basic kinds of information

1) General demographic and health information. This would include such elements as population (age structure and density), pregnancies (fertility rate), births, in- and out-migrations, patterns of health care access and utilization, morbidity (including hospitalizations) and overall and cause-specific mortality.

2) Disease or intervention specific information. DSS also provides an invaluable platform on which to base a range of studies to examine specific disease issues, including descriptive epidemiology, diagnosis, treatment, prevention, behavior, and economics. These studies can take advantage of the sampling frame inherent in a DSS, whether at individual, household/compound or neighborhood level, in that a whole population sample removes many of the biases of other study designs. For example, high quality DSS data are an essential component to assess the impact on mortality of malaria control measures such as IPTi.

From 1996-2001, investigators working at the KEMRI-CDC research station have been conducting a form of demographic surveillance in selected populations. This surveillance activity has been conducted in the context of a large trial examining the immediate and long-term effect of ITNs on all-cause mortality in children. At present, approximately 55,000 persons are under surveillance in the Asembo area. Demographic surveillance has been conducted through biannual house-to-house censuses. Facility-based surveillance at two district hospitals and 6 outpatient clinics in Asembo have provided information on types of illnesses in children in this area that result in health-care seeking behavior and hospitalization. Systematic and continuous entomologic monitoring of anophelines has provided ongoing estimates of the entomologic inoculation rate (EIR); EIR data provide critical information on the intensity of malaria transmission. Ongoing assessment of EIR is necessary to understand if changes in malaria morbidity and mortality are due to an intervention or to natural variation in the intensity of transmission pressure. Complete GIS mapping of the study area has been conducted. Enrollment forms collect information on new residents.

In late 2001, all households and residents in the surveillance area were registered into an upgraded DSS system. Continuous DSS fieldwork is conducted on a 4-month cycle. This cycle begins the first workday of each January, May, and September. Each cycle begins with one week of training, followed by 11 weeks in the field during which every registered household is visited, followed by one week of vacation for the field teams, and finally 4 weeks to resolve discrepancies in the data, catch up with data management and report writing, and conduct special surveys.

During routine DSS interviews, an adult household member is asked about demographic, health and other events within the household. All information is recorded in a household record book and on individual event forms.

To increase accuracy and timeliness of information on births and deaths, every village has a village reporter (VR), a resident who volunteers to report information on every birth or death among households in his/her village.

As part of the DSS activities, there is monitoring of both outpatient (OPD) and inpatient (IPD) visits for children in Asembo. 7 outpatient health facilities, and 2 inpatient facilities have an assigned DSS staff member who interviews all patients and records information onto a standardized form. Children who attend outpatient clinics are linked to the DSS using their permanent IDs cataloged in registers at each health facility. We estimate that approximately 80% of children or their mothers can be linked to their records in the DSS.

## Study population

*Inclusion criteria: Infants attending any one of the 4 study clinics (Abidha, Ongielo, Lwak, and Saradidi or another comparable clinic in Asembo or Gem) for immunization at the 6-week visit will be offered enrollment in the study.*

1. Age 5 weeks to 16 weeks

2. Parent or guardian currently resident in Asembo (or Gem).

3. Parent or guardian has given permission for their child to participate

### Exclusion criteria

1. Known allergy to any of the study drugs

2. Current Cotrimoxazole prophylaxis

3. Concomitant disease requiring hospitalization or transfusion

4. Plans to be away from the study area for more than 6 months during the next year

## Sample Size

This study primarily aims to determine if routine intermittent treatment with antimalarials results in a reduction in childhood clinical malaria, by assessing time to first episode of clinical malaria.

We estimate that the median time to first episode of clinical malaria in the placebo group receiving iron is 18 months (68 weeks after the first intervention visit). The sample size required for 90% power to detect a protective efficacy of 40%, assuming =0.017, is 250 per arm. Alpha has been adjusted to 0.017 in order to account for multiple comparisons (3 arms each compared to the placebo group, Bonferroni adjustment 0.05/3 tests=0.017). Therefore, the study would require a total sample of 1000 infants (250 in each of 4 groups). We expect that 11% of infants will have the outcome measure at baseline and thus will be excluded from the primary analysis. Including this decrease and adjusting for a 10% loss to follow up and 13% mortality, the study will require 1516 infants (379 in each arm).

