**Adverse Event Reporting.**

Adverse Events: Any unexpected medical occurrence in a participant during the trial will be recorded as an adverse event. There are certain events detailed below which are anticipated to have a baseline rate, and are therefore not unexpected. These events will be reported in a summary statement as part of the yearly continuation. If the study team recognizes an increase above an expected rate, the information will be provided earlier than this annual report.

Because the postneonatal infant mortality rate in the IPTi study area is approximately 120 per 1000 infants, it is anticipated that approximately 170 children will die during the course of the study between enrollment (at 6 weeks of age) and the end of the primary study outcome period (at 12 months of age). Therefore, infant deaths from common causes (including malaria, diarrhea, pneumonia, malnutrition, bacterial sepsis, meningitis, other common childhood infections, injuries, prematurity, and congenital conditions) will be considered anticipated adverse events. Hospitalizations from such illnesses will also be considered expected adverse events. Deaths or hospitalizations from unexpected or unusual causes (examples: allergic reactions, non-viral hepatitis, Stevens-Johnson syndrome, toxic epidermal necrolysis, sudden unexplained death) or that in the judgment of the local PI are possibly or probably related to study drug administration will NOT be consideredexpected adverse events, and will be reported to the CDC as outlined below.

Adverse events that are serious, unexpected, and at least possibly related to study drug:

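### The stated 90% power is not met over the 12-month primary window: 250 infants per arm fully followed to 12 months give about 75%, and the sample-size section names no follow-up window

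*Protocol*

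**What the plan says.** The Sample Size section sizes the trial on time to first clinical malaria. It puts the median time to that event "in the placebo group receiving iron is 18 months (68 weeks after the first intervention visit"), and gives 250 per arm as "The sample size required for 90% power to detect a protective efficacy of 40" per cent. It adds that "Alpha has been adjusted to 0.017 in order to account for multiple comparisons", and concludes that "the study would require a total sample of 1000 infants (250 in each of 4 groups"). The 250 is then raised to 379 per arm for 11% excluded at baseline, 10% loss to follow-up and 13% mortality. No length of follow-up, test or sidedness is given.

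Study Design fixes the start of the clock: "IPTi will be provided under supervision at 10 and 14 weeks and again at 9 months". Ten weeks plus 68 weeks is 78 weeks, or 18 months of age, so the median is internally consistent.

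The window is set elsewhere. The primary objective is efficacy "on the prevention of clinical malaria in the first year of life". The Adverse Event Reporting section refers to "the end of the primary study outcome period (at 12 months of age"). Clinic visits continue to 24 months, but nothing extends the primary outcome past 12 months.

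**The concern.** The placebo median lies 26 weeks beyond the close of the primary window (68 weeks against 42). Power for a time-to-event comparison depends on the number of events, so a sample size that relies on events after 12 months overstates power for the first-year question.

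The 90% is the power claim for each of the three comparisons under the only primary objective. If it is too high, a non-significant first-year result for a regimen would be read as stronger evidence against a 40% effect than it is. The protocol's Justification says the results are meant to help direct malaria control policy.

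**Working it through.** **Inputs.** From the Sample Size section: placebo median 68 weeks after the first intervention visit, efficacy 40%, alpha 0.017, power 90%, 250 per arm. From Study Design: first dose at 10 weeks. From the primary objective and Adverse Event Reporting: window closes at 12 months, so 52 − 10 = 42 weeks at risk.

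**Assumptions, not stated in the protocol.** Constant hazard; 40% efficacy read as a hazard ratio (HR) of 0.60, because the outcome is time to first episode; two-sided alpha, so z = 2.387, with 1.282 for 90% power.

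**Events needed per comparison.**
- Schoenfeld: 4 × (2.387 + 1.282)² / (ln 0.60)² = 206.
- Freedman: (2.387 + 1.282)² × (1.60/0.40)² = 215.

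**Event probabilities.** Weekly placebo hazard h = ln 2 / 68 = 0.01019. For T weeks at risk, p0 = 1 − exp(−hT) and p1 = 1 − exp(−0.60hT). The number per arm is the events needed divided by (p0 + p1).

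| Follow-up | p0 | p1 | n per arm, Schoenfeld / Freedman | Events with 250 per arm | Power with 250, Schoenfeld / Freedman |
|---|---|---|---|---|---|
| to 18 months of age (68 wk) | 50.0% | 34.0% | 246 / 257 | 210 | 90.6% / 89.2% |
| to 12 months of age (42 wk) | 34.8% | 22.7% | 359 / 375 | 144 | 75.0% / 72.9% |
| to 24 months of age (94 wk) | 61.6% | 43.7% | 196 / 205 | 263 | 96.1% / 95.3% |

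**The plan's own figure.** On these inputs the 68-week row reproduces 250; the 42- and 94-week rows do not. Two unpooled proportions at 68 weeks give (2.387 + 1.282)² × (0.2500 + 0.2245) / 0.1598² = 250. The attrition step also reproduces: 250 / (1 − 0.11 − 0.10 − 0.13) = 379.

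**Power at 12 months, 250 fully followed.** Φ(√(143.7/4) × 0.5108 − 2.387) = Φ(0.675) = 75.0%. A simulated log-rank test (4,000 runs) gave 74.6%.

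**Power at 12 months, randomised infants with censoring.** After the 11% exclusion, 379 × 0.89 = 337 per arm remain. Assume the 23% deaths and losses accrue exponentially over 42 weeks: loss hazard c = −ln(0.77)/42 = 0.00622. The probability of an observed event is h/(h + c) × (1 − exp(−42(h + c))), with 0.60h in place of h for the drug arm. This gives 30.9% and 20.0%, so 337 × 0.5098 = 172 events. Power is Φ(√(171.8/4) × 0.5108 − 2.387) = 83%. Retaining the 11% as well, 379 per arm give 193 events and 88%.

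**Power at 12 months if 40% is a reduction in cumulative risk.** Risks are 34.8% and 0.60 × 34.8% = 20.9%. Two unpooled proportions need 272 per arm, and 250 give 87% (86% with pooled variance under the null).

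**Efficacy detectable with 90% power, 250 fully followed to 12 months.** Try HR 0.536: p1 = 20.5%, events 250 × (0.348 + 0.205) = 138, and Φ(√(138.3/4) × 0.6236 − 2.387) = 90%. That is about 46% efficacy by Schoenfeld; Freedman is a little higher, so about 46 to 47%.

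**Hazard shape.** Let the cumulative placebo hazard be ln 2 × (42/68)^k, which keeps the 68-week median. The values of k are illustrative. With k = 1.5 (hazard rising with age), 28.6% and 18.3% have an event, giving 117 events and 65% power. With k = 0.8 (falling), 37.6% and 24.6% have an event, giving 156 events and 79% power.

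**The case against.** **The window behind 250 is inferred.** This stands. A reader might infer that 250 can come only from follow-up to 18 months of age, but the protocol does not support that. Counting from birth (52 weeks against a 78-week median) and taking 40% as a risk reduction, the placebo risk is 37.0%, the drug-arm risk 22.2%, and two unpooled proportions give 249 per arm. A risk reading with a 6-week clock, or with one-sided alpha at 42 weeks, also lands near 250. The clock variants set aside the stated count from the first intervention visit, and all of these set aside the time-to-event scale. They are no better documented, but they show that 250 cannot prove which window was used. The shortfall at 12 months does not need that inference: it follows from the stated median, efficacy, alpha and n, with the assumptions listed.

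**75% is not the power of the trial as randomised.** This also stands. A reader might take 75% as the figure for the whole design, but it belongs to 250 infants with complete follow-up. The trial randomises 379 per arm, and an intention-to-treat time-to-event analysis would ordinarily censor deaths and losses at their time at risk. On that basis the figure is about 83%, a gap of about 7 points rather than 15. Exceeding 90% on the hazard-ratio reading would take all 379 with no exclusion, death or loss (218 events, 92%), which contradicts the protocol's own allowances.

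**Mortality window.** A reader might also infer that the 13% mortality covers only the first year, so that losses and events are counted over different periods. The protocol gives no window for it. Its one enrolment-to-12-months figure is about 170 deaths, and 170/1516 = 11.2%, not 13%. That charge is not made here.

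**Constant hazard.** It is an assumption. A falling hazard would raise the 12-month power somewhat; one that rises with age would lower it.

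**Conclusion.** The point holds: the 90% power claim is wrong as written for the protocol's own primary window. Keeping the stated 10-week clock, with two-sided alpha and constant hazard assumed, power for 40% efficacy at 12 months is:

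- about 75% with 250 fully followed infants per arm;
- about 83% with 337 per arm and censored losses (88% if the baseline exclusions are kept);
- about 87% with 250 on a 12-month risk reading.

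The chance of missing a true 40% effect is therefore about 13% to 25%, not 10%. Follow-up to 18 months of age is the reading that best fits the 250 on the stated time-to-event inputs, but it is not established as the one used.

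**What to change.** In the Sample Size section, state the follow-up window, the effect scale of the 40% (hazard ratio or cumulative risk), and the test and sidedness behind the 250. Align them with the primary period from 10 weeks to 12 months of age.

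Replace the unqualified 90% with the power for that window. On a hazard ratio of 0.60 and a stated constant-hazard assumption, this is:

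- about 35% against 23% with an event, and about 144 events per comparison;
- about 75% power for 250 evaluable infants per arm;
- about 83% for the randomised design with deaths and losses censored;
- about 46 to 47% as the efficacy detectable with 90% power at 250.

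The cost is one rewritten paragraph and a less favourable stated power. No extra infants and no change to conduct or analysis are needed.

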**Data Management**

Data cleaning and storage:

Quantitative data will be entered using scan-ready forms and an optical scanner. Data will be entered and edited in Kenya. Images of scan forms will be kept on a secure server with access limited to study personnel. Data analysis will be undertaken collaboratively in Kenya and at CDC in Atlanta. Access to study computers will be restricted to study personnel, and paper records will be secured in locked cabinets in Kenya. Paper records will not be transported to Atlanta. Electronic files will be transferred to Atlanta either as password-protected e-mail attachments or as password protected files on zip disks or CDs.

Sample storage

Specimens will be stored in locked freezers or cabinets with identifiers at KEMRI and at CDC, to which only study personnel will have access.

In accordance with WHO advice, testing for serological responses to EPI antigens will be performed at a single commercial reference laboratory. The commercial laboratory will only have coded specimens, and will not be engaged in the research. Any remaining sera will be shipped back to Kenya.

Statistical analysis:

SAS software (SAS Institute, Cary, NC), and STATA software (STATA corporation, College Station, TX) will be used for quantitative data analysis. The primary analysis will be based on intention to treat. The analysis will be time to first clinical malaria comparing each of the study drug arms to the placebo arm. Mild, moderate, and severe anemia will also be compared between each study drug arm and the placebo arm.

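### The only multiplicity rule stated for the three drug-versus-placebo tests is single-step Bonferroni; it is valid, but Holm's step-down gives more power at the same family-wise 5%

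*Protocol*

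**What the plan says.** The Sample Size section of the protocol sets the level for each comparison: "Alpha has been adjusted to 0.017 in order to account for multiple comparisons". It gives the derivation in brackets: "3 arms each compared to the placebo group, Bonferroni adjustment 0.05/3 tests=0.017". The trial is sized on that level for 90% power at 40% protective efficacy, giving 1000 infants ("250 in each of 4 groups") before inflation to 1516.

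The statistical analysis paragraph under Data Management describes the primary analysis: "The analysis will be time to first clinical malaria comparing each of the study drug arms to the placebo arm". It says the analysis is by intention to treat, but gives no significance level and no multiplicity procedure. The protocol mentions no step-down or other sequential rule. Single-step Bonferroni is therefore the only multiplicity rule that the document states.

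**The concern.** Single-step Bonferroni holds each of the three tests at one third of the overall level, even after another drug has been shown to work. Holm's procedure passes the unused level on. The smallest p-value is tested at 0.05/3. If that is rejected, the next is tested at 0.05/2, and if that is rejected, the last at 0.05. Family-wise error stays at or below 0.05 whichever drugs work, with no added assumption, and every rejection made by Bonferroni at 0.05/3 is kept.

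The difference matters here because the trial needs a verdict on each regimen, not just one success. The section on pharmacokinetic differences and the Justification both plan to read results across regimens with different half-lives, to separate intermittent clearance from prophylaxis and to identify alternatives to SP. When more than one regimen works, fixed Bonferroni leaves a larger chance that an effective one is missed.

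**Working it through.** **Inputs from the Sample Size section:** per-comparison level 0.017; power 90%; protective efficacy 40%, taken as hazard ratio 0.6; placebo median 68 weeks after the first intervention visit; equal allocation to four arms; 11% excluded at baseline, 10% lost and 13% mortality.

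**Assumptions, because the protocol does not state them:** two-sided tests; exponential times; event probabilities taken at 68 weeks; correlation 0.5 between the three test statistics, which follows approximately from equal arms sharing one placebo group.

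**1. The protocol's own figures.**
- Level: 0.05/3 = 0.01667, or 0.017 to three decimals.
- Events per comparison (Schoenfeld): 4(z₁ + z₂)²/(ln 0.6)², with z₁ = 2.387 (two-sided 0.017) and z₂ = 1.282, gives 4 × 3.668²/0.5108² = 206.3, so 207.
- Event probabilities at 68 weeks: placebo 0.500; drug 1 − 0.5^0.6 = 0.340.
- Per arm: 207/(0.500 + 0.340) = 246.4, so 247, against the stated 250.
- Inflation: 250/(1 − 0.11 − 0.10 − 0.13) = 250/0.66 = 378.8, so 379; × 4 = 1516.

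The stated figures reproduce.

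**2. Bonferroni against Holm at the nominal power.** Three normal test statistics with correlation 0.5 were simulated (2,000,000 draws). Each effective drug has mean 2.387 + 1.282 = 3.668, which gives 90% power at 0.017.

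| Scenario | Measure | Bonferroni 0.017 | Holm |
|---|---|---|---|
| No drug works | any false rejection | 0.045 | 0.044 |
| One drug works | power for that drug | 0.900 | 0.900 |
| Two drugs work | power per effective drug | 0.900 | 0.918 |
| Three drugs work | power per drug | 0.900 | 0.942 |
| Three drugs work | all three shown | 0.781 | 0.888 |
| Three drugs work | at least one shown | 0.985 | 0.984 |

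**3. Required size under Holm.** Its first step is 0.05/3, with z₁ = 2.394. Events are 4 × (2.394 + 1.282)²/0.5108² = 207.1, so 208, and 208/0.840 = 247.6, so 248 per arm. The figure of about 250 does not change.

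**4. Effect of the rounding.** 3 × 0.017 = 0.051. Per-drug power is 0.900 at 0.017 and 0.899 at 0.05/3, so rounding up adds about 0.1 point.

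**5. Shorter window.** The primary objective concerns the first year of life. If follow-up for the endpoint ended at 12 months of age, it would run about 52 − 10 = 42 weeks from the first intervention visit. Event probabilities would then be 0.348 and 0.227. With 250 per arm, events per comparison are 250 × 0.575 = 144, and the mean statistic is about 0.5108 × √(144/4) = 3.06. If all three drugs work, power per drug is 75% with Bonferroni and 82% with Holm, and all three are shown in 54% against 70%. With two effective drugs, per-drug power is 75% against 78%. With one, there is no gain.

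**The case against.** The strongest reply is that the document contains no error here. Equal-split Bonferroni is standard and valid, its planning figures reproduce, and its family-wise error is about 4.5%. The level of 0.017 appears only in the sample-size section, and sizing at 0.05/3 is compatible with Holm, whose first step is 0.05/3. A statistical analysis plan, not shown, could already name Holm. All of this stands. It makes the point an optional improvement, and it means that the final tests cannot be said with certainty to use fixed Bonferroni. What remains is that the protocol names one rule and no other.

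The gain also depends on how many drugs work. The protocol does not presume that all three will: the section on pharmacokinetic differences allows that the shorter-acting Lapdap may do less well against anemia, and that the benefit may not appear in this setting. The 4-point and 11-point gains are therefore the favorable case.

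Three stronger readings are tempting and should not be drawn.
- A reader might infer that rounding to 0.017 costs power or breaks error control. It adds about 0.1 point of power. The nominal sum of 0.051 has no practical effect, since the family-wise error is about 4.5%.
- A reader might take 75% as the trial's actual power. That rests on an assumed 42-week horizon, and the Sample Size section states none. If that shortfall is real, it is a separate and larger matter: about 361 per arm would be needed by the same formula (207/0.575), and Holm only partly offsets it.
- A reader might treat step-down Dunnett as the same thing as Holm. It uses the shared-control correlation and different critical values, so it is an alternative and not an equivalent.

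**Conclusion.** The point holds as an inexpensive gain in efficiency, not as a fault in error control. Where at least two regimens are effective, Holm is more powerful than the stated rule at the same family-wise 5%. At the nominal 90% the gain per drug is about 4 points with three equally effective drugs and about 2 points with two. The chance of showing all three rises by about 11 points. Nothing is gained when only one drug works, nothing for the chance of at least one success, and the required number of infants does not fall.

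These sizes rest on two-sided tests, hazard ratio 0.6 for each effective drug and correlation 0.5. That Holm rejects everything that Bonferroni at 0.05/3 rejects depends on none of these assumptions.

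**What to change.** Add one sentence to the Sample Size section or the statistical analysis paragraph: the three primary drug-versus-placebo comparisons are tested by Holm's procedure at a two-sided family-wise level of 0.05, with steps 0.05/3, 0.05/2 and 0.05. Keep 0.05/3 as the level behind the sample-size statement, which stays at about 250 per arm before inflation. Make the change before unblinding, since a later switch would not be credible. If an analysis plan already names a procedure, align the two documents.

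The cost is in the intervals. Bonferroni has simple simultaneous confidence intervals that match its tests, while those matching Holm are less simple. If unadjusted 95% intervals are shown alongside, label them as unadjusted, because one can exclude no effect for a comparison that Holm does not reject.
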